### Study schedule

A summary of the examination procedure for the first, as well as for the following three examination days is shown in Table 3.

**Table 3 T3:** Study schedule.

**Session 1**	**Session 2-4**
**Structural MRI (T1)**	
Navigated TMS	Navigated TMS
RMT/AMT	RMT/AMT
RC	RC
SICI/ICF	SICI/ICF
**Determination of tVNS perception threshold and**	
**discomfort threshold**	
One of the interventions, randomized	One of the interventions, randomized
Verum taVNS (perception threshold)	Verum taVNS (perception threshold)
Verum taVNS (tolerance threshold)	Verum taVNS (tolerance threshold)
Sham taVNS (perception threshold)	Sham taVNS (perception threshold)
Sham taVNS (tolerance threshold)	Sham taVNS (tolerance threshold)
Navigated TMS	Navigated TMS
RMT/AMT	RMT/AMT
RC	RC
SICI/ICF	SICI/ICF

### Outcomes

#### Primary outcome

The primary outcome measurement of cortical excitability will be the post-pre change of SICI in relation to the stimulation method (sham vs. verum).

#### Exploratory outcomes

Exploratory outcome measurements will be the post-pre changes of the TMS parameters (ICF, RMT, AMT, RC), the effect of taVNS intensity on the TMS parameters as well as side effect differences between verum and sham stimulation.

### Statistical analysis

#### Sample size

Overall, only a few studies investigating cerebral motor excitability after taVNS stimulation exist (22–24). Therefore, the determination of the effect size regarding the effect of taVNS on cortical excitability can only be determined inadequately. The total sample size of 30 subjects was determined based on the sample sizes of the mentioned studies (Capone 10 participants, Mertens 15 participants, van Midden 30 participants) (22–24). According to our a priori power analysis using G-Power, this sample size is sufficient to detect small to medium effect sizes (*f* = 0.18) with a power of 0.80.

#### Data analysis

According to our primary outcome measurement, a three-way repeated measure ANOVA with factors time (pre, post), stimulus (verum, sham) as well as stimulus intensity (tolerance, perception threshold) will be performed.

Additional ANOVAs for each exploratory outcome variable will be calculated using the same ANOVA model.

In case of violation of requirements for parametric methods, data will be transformed before analysis or appropriate non-parametric tests will be conducted. Data analysis will be conducted using IBM SPSS Statistics for Windows Version 25 (IBM), MATLAB (MathWorks, 2016) and R software (http://www.R-project.org).

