## Methods and analysis

### Study design

This is a single-center, prospective, double blind, sham-controlled trial evaluating the effect of taVNS on motor cortex excitability. To this end, this study uses four stimulation conditions: taVNS/sham stimulation at perception threshold and taVNS/sham stimulation at tolerance threshold applied in randomized order using a within subject design.

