### Study population and recruitment

In total, 30 subjects will be included in the study. The subjects for the planned study are recruited around the University of Greifswald. The subjects will be recruited for the study by means of a verbal announcement. Due to the time required for the study, all participants will receive an expense allowance of 100 euros after completion of the study for their time.

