### Interventions

The study consists of a structural magnetic resonance imaging (MRI) and of four experimental sessions in total, during which either verum or sham taVNS will be administered at different stimulation intensities. TMS motor physiological measurements will be conducted before and after each taVNS session.

TMS and taVNS will be performed by two administrators (TH or PK). The TMS administrator will be blinded to the taVNS intervention condition (verum or sham), and vice versa. Data collection will take place in the TMS lab. Each measurement (TMS/taVNS) will be performed by only one investigator (TH/PK), with the other investigator being in the room next to the lab to avoid unblinding. The participant will also be instructed to not tell anything about the taVNS to the investigator performing the TMS.

In sum, the administrator applying taVNS will have no knowledge about the TMS parameters. There will be a minimum interval of 1 week between each experimental visit to reduce potential carry-over effects of the previous taVNS.

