#### TMS administration

First, neuronavigation will be performed with a stereo-tactical infrared optical-tracking Polaris camera (Polaris System, Northern Digital, Waterloo, Ontario, Canada) and BrainSight (BrainSight TMS, Rogue Research Inc.). Neuronavigated TMS will be applied via two Magstim 200 stimulators connected to form a BiStim unit (Magstim Company, Dyfed, UK) before and after taVNS application. Here, a figure-of-eight coil (70 mm in wing diameter) will be held tangentially over the scalp with orientation of the handle angled 45 degrees in the sagittal plane. The coil will be positioned that a maximum-evoked motor evoked potential (MEP) can be derived (motor hotspot). The cortical area stimulated by the TMS coil will be digitally marked on the MRI and stored in the neuronavigation program to guarantee precise, navigation-based stimulation on all examination days. Baseline TMS will take place on each experimental visit day, followed by verum or sham taVNS and will be repeated immediately after taVNS administration.

Surface electromyography (EMG) will be derived over the right and left interosseus dorsalis I muscles using Ag/AgCl electrodes (Ambu, Ballerup, Denmark) measuring 10 mm in diameter. The EMG signal will be amplified (CED 1902; Cambridge Electronic Design, Cambridge, United Kingdom), band-pass filtered (20–1,000 Hz), recorded with a temporal resolution of 2 kHz (CED 1401), and stored for off-line analyses (Signal V4.09). During the TMS examination, the patient will sit relaxed in an examination chair while the hand will be positioned on a pillow for measuring. Measurements from the EMG will be used to assess motor physiology.

The following motor physiology outcome measures will be collected: resting motor threshold (RMT), active motor threshold (AMT), input-output curve [recruitment curve; (RC)], short intracortical inhibition (SICI), intracortical facilitation (ICF).

The RMT is the minimum applied stimulation intensity to derive MEPs with at least a 50 μV amplitude level in four out of eight trials in relaxation.

The AMT is the minimum-applied stimulation strength to derive visible MEPs in four out of eight trials with minimal tension on the target muscle (abduction of the index finger) with ~100 μV EMG.

For evaluation of the RC, 10 × stimulation each at an intensity of 90, 100, 110, 120, 130, 140, 150, and 160% RMT will be presented in an pseudorandomized order.

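### The primary ANOVA is valid but analyses change scores; adjusting for the SICI baseline taken at every session would usually estimate the same effect more precisely

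*Protocol article*

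**What the plan says.** The Primary outcome section names "the post-pre change of SICI in relation to the stimulation method (sham vs. verum" as the confirmatory comparison. The Data analysis section tests it with "a three-way repeated measure ANOVA with factors time (pre, post), stimulus (verum, sham) as well as stimulus intensity". The effect of interest is therefore the time-by-stimulus interaction, averaged over the two intensities.

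The four conditions are "applied in randomized order using a within subject design", and the Interventions section sets the spacing: "There will be a minimum interval of 1 week between each experimental visit". Under TMS administration, "Baseline TMS will take place on each experimental visit day, followed by verum or sham taVNS", so each participant contributes four session-specific baselines.

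On size: "In total, 30 subjects will be included in the study". The Sample size section cites a G*Power calculation with f = 0.18 and power 0.80. The article names no baseline covariate and no mixed model. It states no rule for a missed session, and the Randomization section expects every participant to complete all four conditions.

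**The concern.** When pre and post are two levels of a time factor, the interaction test uses post minus pre as its outcome. That is the best use of the baseline only if the slope of post on pre within participants, across sessions, is close to 1. If the slope is lower, the part of the baseline noise that is not shared with the post measurement is added to the outcome. Each SICI value rests on 15 conditioned and 15 unconditioned pulses, so a slope below 1 is plausible. That is a judgement; the article gives no reliability figure.

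At stake is precision on the trial's single confirmatory comparison, in a study whose authors say that the effect size could be determined only inadequately. A lesser matter is that a classical repeated-measures ANOVA needs all eight cells from each participant.

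**Working it through.** **1. The plan's own figure.** Alpha, the number of measurements, the correlation and epsilon are not stated; I assume alpha 0.05, correlation 0.5 and epsilon 1. For G*Power's within-factor test, λ = f²·N·m/(1−ρ), with m−1 and (N−1)(m−1) df.
- m = 8: λ = 0.0324 × 30 × 8 / 0.5 = 15.55; power 0.82; detectable f at N = 30 is 0.176, which rounds to 0.18. The stated figure reproduces.
- m = 4: λ = 7.78; power 0.62.
- m = 2: λ = 3.89; power 0.48.

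At this correlation the figure matches an eight-level, 7-df test. The article does not show 0.80 for the 1-df primary test.

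**2. The primary test is a change-score test.** On simulated data with 30 participants and all eight cells, F(time × stimulus) = 2.0650 on (1, 29) df. The squared t of the paired verum-sham contrast of changes is also 2.0650.

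**3. Variance ratio with a common response.** Let s² be the within-participant variance of the contrast at either time. The change score has variance 2s²(1−r) and the adjusted contrast s²(1−r²). The ratio is (1−r²)/[2(1−r)] = (1+r)/2. Estimating the slope from 30 participants costs a factor 1 + 1/27 = 1.037.

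| r (assumed) | (1+r)/2 | × 1.037 | simulated |
|---|---|---|---|
| 0.3 | 0.65 | 0.67 | 0.67 |
| 0.5 | 0.75 | 0.78 | 0.78 |
| 0.7 | 0.85 | 0.88 | 0.88 |
| 0.9 | 0.95 | 0.985 | 0.99 |

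If the change-score test did have power 0.80 (a standardised paired effect of 0.529 at n = 30), the adjusted test would have 0.93, 0.89, 0.85 and 0.81. These powers are conditional on that starting value.

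**4. Participants who respond differently.** Give the individual verum-sham response an SD of τ, in units of s. This adds τ² to both variances, so the ratio is 1.037 × [(1−r²)+τ²]/[2(1−r)+τ²].
- r = 0.5, τ = 0.5: 1.037 × 1.00/1.25 = 0.83.
- r = 0.5, τ = 1: 1.037 × 1.75/2.00 = 0.91.
- r = 0.7, τ = 1: 1.037 × 1.51/1.60 = 0.98.
- r = 0.9, τ = 0.5: 1.037 × 0.44/0.45 = 1.01.
- r = 0.9, τ = 1: 1.037 × 1.19/1.20 = 1.03.

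So the gain shrinks, and at high r there is a loss of about 1-3%.

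**5. Type I error of possible replacements.** These are simulations under a null mean effect with N = 30 and r = 0.3 to 0.7.
- Planned ANOVA: 0.04 to 0.06 throughout.
- Mixed model with a random participant intercept only: about 0.05 at τ = 0, 0.07 to 0.08 at τ = 0.5, and 0.11 to 0.15 at τ = 1.
- Baseline-adjusted regression on each participant's own verum-sham contrast: held 0.05.

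**6. Form of the baseline.** In a random-intercept model, a single raw baseline mixes within- and between-participant slopes. At r = 0.1, with the between-participant SD twice the within-participant SD, the variance ratio was 0.79. Splitting the baseline into participant mean and within-participant deviation gave 0.57.

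**7. Missed sessions.** If whole participants were dropped, a change-score power of 0.80 would fall to 0.75 with 3 lost and 0.70 with 6 lost. With 3 partial completers, an unadjusted mixed model that kept their sessions had a variance ratio of 0.96 to 0.97. Nearly all of the benefit therefore comes from the baseline adjustment.

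**The case against.** The strongest reply is that nothing here is wrong. The primary outcome is defined as a change, and the ANOVA tests exactly that change. It also uses each participant's own verum-sham difference as its error term, so it stays valid when people respond differently to stimulation. All of this stands. A replacement that gave up that protection would be worse than the plan, as the type I error figures for the intercept-only model show. Kenward-Roger df do not make up for an omitted variance component.

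It also stands that the size of the gain is unknown. No value of r is given, and near r = 0.9 there is little or nothing to win.

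A reader might go on to infer that the plan discards every participant with a missed visit. The article does not say so. The restriction follows from the classical method, and a rule for missed sessions may well sit in a document not shown. A reader might also infer that adjustment lifts this trial's power from 0.80 to above 0.90. The article does not support that either, because the 0.80 is not shown for the 1-df test and the rise depends on an assumed r.

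The objection does not remove the main point. The baselines are already collected, they precede stimulation on the day, and adjusting for them leaves the estimated effect unchanged.

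**Conclusion.** The point holds as an efficiency improvement. The planned ANOVA is valid and unbiased, but it fixes the baseline slope at 1 when the slope could be estimated from data already in the schedule. With 30 participants and a common response, the variance falls by about 33%, 22%, 12% and 1% for r = 0.3, 0.5, 0.7 and 0.9. The fall is smaller if individual responses vary, and at high r it can turn into a loss of about 1-3%. Both r and the spread of individual responses are assumptions. Keeping partial completers is a small secondary benefit.

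**What to change.** Define the primary estimate as the baseline-adjusted verum-minus-sham difference in post-session SICI, averaged over the two intensities. Either form will do:

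- **Participant-level regression.** Regress each participant's verum-sham difference in post-session SICI on the same participant's verum-sham difference in baseline SICI. Read the effect as the intercept at a baseline difference of zero. Do not centre that difference on its own sample mean: the intercept would then be the plain mean post difference, and the adjustment would be lost.
- **Linear mixed model of post-session SICI.** Use fixed effects for stimulus, intensity, their interaction, session, and baseline split into participant mean and within-participant deviation. Add a random participant intercept and a random participant-by-stimulus term, with Kenward-Roger df. The participant-by-stimulus term is essential. This form also keeps the completed sessions of anyone who misses a visit.

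Name one form as primary in advance and keep the planned ANOVA as a sensitivity analysis. The cost is a change of wording and one or a few df. R is already listed among the software, and no data collection changes.

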## Discussion

To date, there has been a gap in understanding whether taVNS modulates cortical excitability and its underlying mechanism. For the first time, this prospective trial will investigate the effects of taVNS on motor cortex excitability as well as on distinct GABAergic and glutamergic pathways in human motor cortex in a double blinded, SHAM controlled, study design.

Non-invasive taVNS is a widely used method in biopsychological research with increasing evidence of effectiveness also in neurological diseases [for a review see for example Yap et al. (3) and (31)]. Interestingly, several studies focused on motor outcome parameters, for example in stroke research (26–30), but only a very few studies have been conducted to investigate the influence of taVNS on cortical excitability itself (22–24).

There is a high methodological heterogeneity between these previous studies regarding the taVNS protocol, different number of participants, as well as different methods for data analysis, which significantly impairs the generalizability of the results.

We will conduct this study to broaden the knowledge about the modulatory effect of taVNS. We will also reach a high data quality using a prospective, double blind, randomized, sham-controlled within subject trial with taVNS at different intensities. Our results will help to understand the physiological role of vagus nerve stimulation on the motor system itself, which makes it possible to better understand the application of this method in neurological conditions like stroke.

## Ethics statement

The studies involving humans were approved by Ethics Committee of the University Medical Center Greifswald (study reference number: BB048/22). The studies were conducted in accordance with the local legislation and institutional requirements. The participants provided their written informed consent to participate in this study.
